## Abstract

**Introduction:**

Pressure injuries (PIs) remain a common and costly complication among critically ill patients despite advances in prevention strategies. Current assessment methods rely primarily on visual skin inspection and risk assessment tools, which may fail to detect early physiological alterations preceding visible tissue damage. Biophysical parameters, including transepidermal water loss, stratum corneum hydration, skin pH and skin temperature, have emerged as promising indicators of skin barrier dysfunction; however, longitudinal evidence in intensive care populations remains limited. This study aims to investigate temporal changes in skin barrier function in pressure injury-prone and affected skin and to identify clinical and physiological factors associated with skin barrier dysfunction and pressure injury development.

**Methods and analysis:**

The SKIN-BAR project is a prospective observational cohort study to be conducted in an adult intensive care unit in Turkey. A total of 165 critically ill adults will be recruited and followed throughout their intensive care unit (ICU) stay. Skin barrier function will be assessed using non-invasive measurements of transepidermal water loss, stratum corneum hydration, skin pH and skin temperature. Measurements will be obtained within the first 4 hours of ICU admission, at 24, 48, 72 and 96 hours, on day 14, and weekly thereafter until ICU discharge. Clinical, laboratory, treatment-related and nursing care variables will also be collected. Linear mixed-effects models will be used to examine longitudinal changes in skin barrier function, while discrete-time survival analysis will be used to evaluate factors associated with incident pressure injury development.

**Ethics and dissemination:**

Ethical approval has been obtained from the Institutional Research Ethics Committee. Written informed consent will be obtained from participants or their legally authorised representatives before enrolment. Findings will be disseminated through publication in peer-reviewed journals, presentations at national and international scientific conferences and other academic dissemination activities.

**Trial registration number:**

NCT07560683.

STRENGTHS AND LIMITATIONS OF THIS STUDYThis prospective observational cohort study will provide repeated longitudinal measurements of multiple objective skin barrier function parameters, including transepidermal water loss, stratum corneum hydration, skin pH and skin temperature throughout the intensive care stay.Standardised non-invasive biophysical measurements combined with comprehensive clinical, laboratory and nursing data will enable detailed evaluation of factors associated with skin barrier dysfunction and pressure injury development.The longitudinal design allows assessment of temporal changes in skin barrier function before and after pressure injury development, which has been insufficiently explored in previous studies.As a single-centre study conducted in one adult intensive care unit, the findings may have limited generalisability to other healthcare settings and patient populations.The observational design allows investigation of associations but does not permit causal inference regarding skin barrier alterations and pressure injury development.

## Introduction

 Pressure injuries (PIs) are localised tissue damages that typically develop over bony prominences as a result of prolonged pressure or the combined effect of pressure and shear forces on the skin and/or underlying soft tissue.^1
^Patients monitored in intensive care unit (ICU) constitute a particularly high-risk group for PIs due to factors such as immobility, hypoperfusion, vasopressor use, inadequate nutrition, mechanical ventilation, invasive devices, fluid and electrolyte imbalances and haemodynamic instability, all of which reduce tissue tolerance and accelerate PI development.^2^

The prevalence and incidence of PIs acquired in intensive care settings remain substantial worldwide. In the DecubICUs study, PIs were identified in 6747 of 13 254 patients followed in 1117 ICUs, with 59.2% of these lesions developing during ICU stay.^3^ In addition to their clinical consequences, PIs impose a considerable economic burden on healthcare systems.^4–7^

The prevention and early detection of PIs are recognised as key indicators of nursing care quality. Current clinical guidelines recommend evidence-based interventions including risk assessment, comprehensive skin evaluation, protective skin care, regular repositioning, early mobilisation, nutritional support and the use of pressure-redistributing support surfaces.^1
8^ Among these strategies, skin assessment plays a central role in identifying early tissue damage and guiding preventive interventions.^9^ However, visual skin assessment remains dependent on clinician judgement and may be subject to variability, potentially limiting the objectivity and sensitivity of findings.^10^

Consequently, increasing attention has been directed toward objective approaches for assessing skin barrier function. Biophysical measurements obtained through biosensory technologies suggest that PI pathophysiology, including ischaemia, reperfusion injury, cellular death, inflammation and impaired lymphatic drainage, may be reflected by alterations in skin barrier integrity before visible clinical signs emerge.^11
12^ Parameters commonly associated with skin barrier function include transepidermal water loss (TEWL), skin pH, subepidermal moisture, stratum corneum hydration (SCH), erythema, skin temperature, sebum and transcutaneous oxygen levels.^13–16^

Although previous studies suggest that changes in biophysical parameters may indicate early impairment of the skin barrier, existing evidence remains fragmented. Most studies have focused on single parameters, included limited sample sizes, evaluated a restricted number of anatomical sites or lacked repeated measurements, particularly in critically ill populations.^17–19^ As a result, the longitudinal relationship between skin barrier function and PI development remains insufficiently understood.

To address these gaps, the SKIN-BAR project was designed to investigate skin barrier function in PI-prone and affected anatomical sites among ICU patients using repeated, non-invasive biosensor-based measurements. By integrating multiple biophysical parameters with detailed clinical data, this study aims to improve understanding of skin barrier alterations associated with PI development and to support the future identification of objective physiological markers for early PI detection and prevention.

### Objectives

This study aims to investigate skin barrier function in PI-prone and affected anatomical sites among ICU patients using non-invasive assessments of TEWL, skin pH, stratum corneum hydration and local skin temperature. Specifically, the study will evaluate longitudinal changes in skin barrier parameters, compare patients with and without PIs, examine relationships between biophysical measurements, identify clinical and physiological determinants of skin barrier dysfunction and explore differences according to PI stage and anatomical location.

## Methods and analysis

### Study design and setting

This study is designed as a prospective longitudinal cohort study conducted in an intensive care setting. The research will be carried out in the adult ICU of Koç University Hospital, Department of Anesthesiology and Reanimation in Turkey. The study is planned over a total period of 24 months, commencing in September 2026 and concluding in September 2028.

### Participants and sampling

All patients admitted to the ICU during the study period who meet the eligibility criteria will be invited to participate. Eligible patients who provide informed consent, either directly or via a legal representative, will be consecutively enrolled and followed longitudinally throughout their ICU stay.

The sample size was calculated using G*Power software based on previously reported differences in sacral stratum corneum hydration between patients who developed PIs and those who did not. In the reference study, sacral stratum corneum hydration was 17.7±3.78 AU in patients who developed pressure injuries and 20.0±3.92 AU in those who did not, corresponding to an effect size of approximately Cohen’s d=0.59.^20^ Assuming a two-sided significance level of 0.05, 90% statistical power and an allocation ratio of 1:2 based on the expected distribution of patients with and without pressure injury in the study setting, the minimum required sample size was calculated as 138 participants (46 with PI and 92 without PI). To account for an anticipated attrition rate of approximately 20%, the target sample size was increased to 165 participants.

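### The 20% attrition allowance was multiplied on instead of divided out: 165 recruits leave 132, not 138, and power is about 89% rather than 90%

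*Protocol article*

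**What the plan says.** The sample size paragraph (Protocol article, Participants and sampling) rests on one comparison, sacral stratum corneum hydration in patients who do and do not develop a pressure injury (PI). In its reference study, "sacral stratum corneum hydration was 17.7±3.78 AU in patients who developed pressure injuries and 20.0±3.92 AU in those who did not", which the article describes as "corresponding to an effect size of approximately Cohen’s d=0.59". The design inputs are given as "Assuming a two-sided significance level of 0.05, 90% statistical power and an allocation ratio of 1:2". From these, "the minimum required sample size was calculated as 138 participants (46 with PI and 92 without PI".

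The attrition step follows: "To account for an anticipated attrition rate of approximately 20%, the target sample size was increased to 165 participants". The abstract, under Methods and analysis, repeats the target: "A total of 165 critically ill adults will be recruited". No other section gives a different attrition rate or another rule for the inflation.

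**The concern.** Attrition is a fraction of the patients recruited, so the recruitment target is the required number divided by the fraction expected to remain. Multiplying the required number by one plus the attrition rate gives too small a target. The figure of 165 looks like the result of that multiplication. If so, the article says that it has allowed for 20% attrition when the target covers less, and the number it calls the minimum would not be reached under its own assumption. At stake is whether the stated combination of 90% power, 20% attrition and 165 recruits is true as printed.

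**Working it through.** **Inputs**, all from Participants and sampling: means 17.7 and 20.0 AU, SDs 3.78 and 3.92, d = 0.59, two-sided alpha 0.05, power 90%, ratio 1:2, required N 138, attrition about 20%, target 165.

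**1. Effect size.** The difference is 20.0 − 17.7 = 2.3 AU. The root-mean-square SD is √((3.78² + 3.92²)/2) = 3.85, so d = 2.3/3.85 = 0.597. With the SDs pooled 1:2, d = 0.594. Both agree with the stated value of approximately 0.59.

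**2. The article's base figure.** By the normal approximation, the PI group needs (1 + 1/2) × ((1.960 + 1.282)/0.59)² = 45.3, so 46, with 92 in the other group and 138 in total. The exact noncentral t calculation also gives 46 + 92, with power 90.05%. One PI patient fewer (45 + 90) gives 89.4%. So 138 is reproduced, and at d = 0.59 it has no slack.

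**3. The attrition step.**
- Multiplying: 138 × 1.20 = 165.6, which is 165 when rounded down. This reproduces the printed target.
- Dividing: 138 / (1 − 0.20) = 172.5, so 173. Check: 173 × 0.80 = 138.4.

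**4. What 165 delivers.**
- At 20% attrition: 165 × 0.80 = 132, or 44 with PI and 88 without at 1:2. This is 138 − 132 = 6 below the minimum.
- Largest loss that still leaves 138: 1 − 138/165 = 27/165 = 16.4%.
- Shortfall against the divided target: 173 − 165 = 8, and 8/173 = 4.6%.

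**5. Power** (noncentral t, two-sided 0.05, d = 0.59, 1:2 split):

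| Attrition from 165 | Evaluable | Power |
|---|---|---|
| 15% | 140.25 | 90.5% |
| 16% | 138.6 | 90.2% |
| 18% | 135.3 | 89.5% |
| 20% | 132 | 88.7% |
| 25% | 123.75 | 86.6% |

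**6. Sensitivity to rounding of d.** With the unrounded d = 0.597, the requirement falls to 135 (45 + 90) and power at 132 is 89.5%. Even then 132 is below the requirement, and the target at 20% attrition would be 135/0.80 = 168.75, so 169. Rounding of d does not reconcile the figures.

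**The case against.** The best defence is that the error hardly matters, and most of that stands. The loss is 0.5 to 1.3 percentage points of power, depending on how d is rounded. The comparison that sets the sample size is listed under Exploratory outcomes. The Statistical analysis section makes linear mixed-effects models the primary approach to change over time, and patients with incomplete follow-up still contribute to them. Death and ICU discharge before PI are treated as competing events, so those patients are not simply lost. Treating every patient lost to attrition as contributing nothing is therefore a planning convention, and the real loss of information may be smaller.

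A second defence is the word approximately. It does not help. The match to 138 × 1.20 shows that 20% was the rate used, and a reader could not tell that about 16% is the rate covered.

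Three stronger readings are tempting, and the documents do not support them:

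- *The study is seriously underpowered.* A reader might point to lower power if fewer than one third develop a PI: with 132 retained, about 83% at 25% incidence and 76% at 20%. Almost all of that drop comes from the change in incidence. With all 138 retained the figures are already 84.6% and 78.6%. Those incidences are assumptions, whereas the article describes its ratio as "an allocation ratio of 1:2 based on the expected distribution of patients with and without pressure injury in the study setting". The basis for that is not shown, so it cannot be called wrong.
- *The Introduction implies an incidence of about 30%.* That comes from multiplying a proportion of patients by a proportion of lesions across 1117 ICUs. It is not an estimate for one ICU that enrols only patients with intact skin.
- *The survival model falls below the events it needs.* The 46 was derived for a comparison of two means and is no threshold for that model. The Statistical analysis section already ties the number of covariates to the events observed.

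**Conclusion.** The attrition step is wrong as written, and the error is minor. The three printed figures (138, about 20%, 165) cannot all hold. Under the article's own assumptions, 132 participants remain and power is about 89% (88.7%) rather than 90%. The target of 165 keeps 138 only if attrition is no more than about 16%. The base calculation of 138 is correct. These figures assume d = 0.59, a 1:2 split that still holds among those retained, and no contribution from patients lost to attrition. The error does not threaten the study or alter any planned analysis.

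**What to change.** Either of two corrections would do. The Study status section says that recruitment has not begun, so both can still be made in advance.

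1. **Keep 165 and restate the sentence** in Participants and sampling, for example: *With 20% attrition, 132 participants (44 with PI, 88 without) give about 89% power; 165 preserves 90% power for attrition up to about 16%.* This costs one sentence and a slightly less favourable power figure.
2. **Keep both 90% power and 20% attrition, and state the target as 173** in Participants and sampling and in the abstract. This costs 8 more patients (4.6% of 173).

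The first is enough, given the size of the effect.

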### Eligibility criteria

Participants will be included if they are aged 18 years or older, undergo initial assessment within the first 4 hours of ICU admission, are haemodynamically stable to tolerate repeated measurements and have intact skin integrity at ICU admission. Written informed consent will be obtained from all participants or their legally authorised representatives.

Patients will be excluded if they are unable to tolerate position changes, are in the post-cardiopulmonary resuscitation period at enrolment, experience cardiac arrest requiring resuscitation during follow-up, have severe oedema or subcutaneous fluid accumulation, present with pre-existing skin lesions prior to ICU admission or have systemic dermatological conditions that may directly affect skin barrier function.

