#### Secondary outcomes

Secondary outcomes include PI incidence, time to PI development and PI severity according to the NPIAP, EPUAP and PPPIA classification system. Among patients who develop PIs, wound progression and healing status will be evaluated using the Bates-Jensen Wound Assessment Tool. Additional secondary outcomes include ICU length of stay and ICU mortality.

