#### Statistical analysis

Statistical analyses will be performed using IBM SPSS Statistics V.29.0 and, where required for time-to-event analyses, R statistical software.

Descriptive statistics will be used to summarise demographic, clinical and skin barrier function characteristics. Prior to inferential analyses, data will be examined for completeness, outliers and distributional assumptions. Continuous variables will be assessed for normality using visual inspection methods (histograms and Q–Q plots) and the Shapiro-Wilk test. Descriptive statistics will be reported as mean and SD or median and IQR, as appropriate. Continuous variables will be reported as mean and SD or median and IQR, as appropriate, whereas categorical variables will be presented as frequencies and percentages.

Changes in TEWL, SCH, skin pH and local skin temperature over time will be examined using repeated-measures analyses. To account for repeated observations within individuals and varying follow-up durations, linear mixed-effects models will be used as the primary analytical approach.

Comparisons between patients who develop PIs and those who do not will be performed using appropriate parametric or non-parametric methods according to data distribution. For patients who develop PIs, measurements obtained from affected sites will be compared with corresponding control sites using paired analyses.

The association between longitudinal skin barrier function parameters and incident PI development will be evaluated using discrete-time survival analysis. Follow-up will be divided according to the predefined skin assessment intervals, thereby accounting for the interval-censored nature of PI onset. TEWL, SCH, skin pH and local skin temperature will be incorporated as time-varying covariates using the most recent measurement available for each assessment interval. Death and ICU discharge before PI development will be considered competing events and will be explicitly accounted for in the time-to-event analyses. Potential determinants, including demographic characteristics, illness severity, PI risk scores, laboratory findings, treatments and nursing care practices, will first be examined in univariable analyses. Multivariable models will subsequently be constructed using a limited number of prespecified clinically relevant covariates, according to the number of observed PI events, to minimise model overfitting.

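### An arrest during follow-up is listed as an exclusion criterion, so enrolled patients leave the cohort on a post-enrolment event and ICU mortality is likely to be understated

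*Protocol article*

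**What the plan says.** All references are to the protocol article.

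- **Eligibility criteria.** The exclusion list has two resuscitation clauses. One concerns patients who "are in the post-cardiopulmonary resuscitation period at enrolment". The other concerns patients who "experience cardiac arrest requiring resuscitation during follow-up".
- **Participants and sampling.** Eligible consenting patients will be "consecutively enrolled and followed longitudinally throughout their ICU stay".
- **Secondary outcomes.** "Secondary outcomes include PI incidence, time to PI development and PI severity"; further on, "Additional secondary outcomes include ICU length of stay and ICU mortality". Table 1 schedules ICU mortality to be recorded at ICU discharge or death.
- **Statistical analysis.** "Death and ICU discharge before PI development will be considered competing events and will be explicitly accounted for in the time-to-event analyses".

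The article does not say whether data collected before an arrest are kept, whether vital status is still recorded afterwards, or how these patients enter the mixed models or the discrete-time survival model.

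**The concern.** An exclusion criterion should be decidable when the patient enters the study. Because the article has a separate clause for the state at enrolment, the follow-up clause cannot be a loosely worded baseline condition. It can apply only to someone already in the cohort.

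The event is also not neutral. Cardiac arrest is closely tied to death, which the plan uses both as an outcome and as a competing event. The Introduction names hypoperfusion, vasopressor use and haemodynamic instability among the factors that promote PI, so arrest may be related to PI risk and to the barrier readings as well. At stake are the ICU mortality estimate, the competing-event part of the time-to-event analysis and, less certainly, PI incidence and the barrier trajectories.

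**Working it through.** **The plan's own figure.** The sample size reproduces: a two-sample t-test with d = 0.59, two-sided alpha 0.05, 90% power and 1:2 allocation gives 46 + 92 = 138 (power 0.9005). The point here does not depend on it. The figure serves only to supply the planned PI proportion, 46/138 = 33.3%, and the target cohort of 165.

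**Step 1: what the clause can mean.**

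| Reading of the exclusion | What is lost | Statistical consequence |
|---|---|---|
| Removal from the cohort | Readings and PI events before the arrest; deaths after it | Cohort conditioned on a future event |
| Withdrawal at the arrest, earlier data kept | Deaths and PIs after the arrest | Informative loss to follow-up |

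Neither fits follow-up of every enrolled patient throughout the ICU stay.

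**Step 2: effect on ICU mortality.** Let m be true ICU mortality, a the proportion with an arrest, and f the risk of death among them. None of these is given in the article, so all are assumptions.

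- Arrest patients out of numerator and denominator: (m − a·f)/(1 − a). This is below m exactly when f > m.
- Arrest patients kept in the denominator but their deaths unrecorded: m − a·f.

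With m = 20% and f = 80% in 165 patients (33 deaths):

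| a | Arrest patients (165·a) | Deaths lost (165·a·f) | Removed: (m − a·f)/(1 − a) | Relative shortfall | Unrecorded: m − a·f |
|---|---|---|---|---|---|
| 3% | 5.0 | 4.0 of 33 | 0.176/0.97 = 18.1% | 9% | 17.6% |
| 5% | 8.3 | 6.6 of 33 | 0.160/0.95 = 16.8% | 16% | 16.0% |
| 8% | 13.2 | 10.6 of 33 | 0.136/0.92 = 14.8% | 26% | 13.6% |

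Under other assumptions with removal, a true mortality of 25% with f = 80% becomes 23.3% at a = 3%, 21.5% at 6% and 18.9% at 10%. Over m = 15–35%, a = 3–10% and f = 60–100%, the relative shortfall runs from about 2% to 63%. The direction is constant; the size depends almost wholly on the assumed rates.

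**Step 3: effect on PI incidence.** Let p = 33.3% and let q be PI incidence among arrest patients (assumed). After removal, incidence is (p − a·q)/(1 − a).

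- a = 10%, q = 60%: (0.333 − 0.060)/0.90 = 30.4%
- a = 10%, q = 20%: (0.333 − 0.020)/0.90 = 34.8%
- q = 33.3%: no change at any a

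The shift is smaller than for mortality and can go either way.

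**Step 4: the competing event.** The plan counts death before PI. Any arrest patient who is free of PI and then dies is such an event, and under either reading it can drop out. The cumulative incidence of death before PI is then understated on the same condition as in Step 2.

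**The case against.** The best defence is that the clause is a discontinuation rule placed in the wrong list. The article says only that such patients are excluded; it does not say that collected data are discarded. It budgets for attrition and chooses mixed models partly because follow-up lengths vary, and both are compatible with keeping data up to the arrest. A condensed article also commonly leaves the handling of discontinued patients to the full protocol or analysis plan.

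Part of this stands. A reader might infer that valid pre-arrest readings and earlier PIs are certainly deleted, and that immortal-time type selection therefore follows. The text does not establish that; it holds only under the removal reading. A reader might also infer that PI incidence is biased, probably downwards. Step 3 does not support that: the direction is undetermined and the bias is nil if arrest patients have average PI risk. Nor does the clause touch deaths without attempted resuscitation, and no effect on the four primary skin parameters has been quantified.

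The defence does not rescue the clause. Withdrawal at the arrest still loses later deaths, and selectively. The only harmless reading is that skin readings stop while outcomes continue to be recorded, and the article does not say this. The objection is to a rule that the article states, not to a detail it omits; an analysis plan cannot recover outcomes that were never collected.

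**Conclusion.** The clause is wrong as written. It applies a post-enrolment event as an exclusion and contradicts the article's own follow-up, outcome and competing-risk statements.

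ICU mortality and the competing event of death are understated whenever arrest patients die more often than the rest. The illustration (20% falling to between 18.1% and 14.8% for arrest rates of 3% to 8%) rests on an assumed 20% ICU mortality and 80% death after arrest, and shows scale only. Bias in PI incidence and barrier trajectories is possible, with unknown direction and size. Which data would be lost depends on whether exclusion means removal or withdrawal, which the article leaves open.

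**What to change.** 1. In Eligibility criteria, limit the exclusion list to conditions known at enrolment. The clause on the post-resuscitation state at enrolment already meets this; the follow-up clause should come out of the list.
2. State that every enrolled patient, with all data up to an arrest, stays in the analysis set.
3. State that ICU discharge, death and, where routine records allow, PI status continue to be recorded after an arrest.
4. Whether skin readings continue after an arrest stays with the investigators. If they stop, treat later readings as missing in the mixed models. In the discrete-time competing-risk model, carry arrest as a time-varying covariate. Use censoring at the arrest only as a sensitivity analysis, because that censoring is itself informative.

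The cost is about one sentence in the eligibility section and a sentence or two on follow-up and analysis, with no extra patients or device readings. The small downside is that PI status taken from charts may be less complete than study assessments, which should be acknowledged. Recruitment had not begun when the article was submitted, so the change can be made before any outcome is lost.
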